## Abstract

**Background:**

Obesity in infertile women increases the costs of fertility treatments, reduces their effectiveness and increases significantly the risks of many complications of pregnancy and for the newborn. Studies suggest that even a modest loss of 5–10 % of body weight can restore ovulation. However, there are gaps in knowledge regarding the benefits and cost-effectiveness of a lifestyle modification program targeting obese infertile women and integrated into the fertility clinics. This study will evaluate clinical outcomes and costs of a transferable interdisciplinary lifestyle intervention, before and during pregnancy, in obese infertile women. We hypothesize that the intervention will: 1) improve fertility, efficacy of fertility treatments, and health of mothers and their children; and 2) reduce the cost per live birth, including costs of fertility treatments and pregnancy outcomes.

**Methods/Design:**

Obese infertile women (age: 18–40 years; BMI ≥30 kg/m^2^ or ≥27 kg/m^2^ with polycystic ovary syndrome) will be randomised to either a lifestyle intervention followed by standard fertility treatments after 6 months if no conception has been achieved (intervention group) or standard fertility treatments only (control group). The intervention and/or follow-up will last for a maximum of 18 months or up to the end of pregnancy. Evaluation visits will be planned every 6 months where different outcome measures will be assessed. The primary outcome will be live-birth rates at 18 months. The secondary outcomes will be sub-divided into four categories: lifestyle and anthropometric, fertility, pregnancy complications, and neonatal outcomes. Outcomes and costs will be also compared to similar women seen in three fertility clinics across Canada. Qualitative data will also be collected from both professionals and obese infertile women.

**Discussion:**

This study will generate new knowledge about the implementation, impacts and costs of a lifestyle management program in obese infertile women. This information will be relevant for decision-makers and health care professionals, and should be generalizable to North American fertility clinics.

**Trial registration:**

ClinicalTrials.gov NCT01483612. Registered 25 November 2011.

## Background

### Obesity and fertility

Infertility affects approximately 10–15 % of couples [1]. One of the leading causes in women is anovulation caused by the polycystic ovary syndrome (PCOS) [2, 3], which affects 6–10 % of women of childbearing age [4]. PCOS accounts for more than 70 % of anovulatory infertility in women [5]. This syndrome is defined by hyperandrogenism and anovulation/polycystic ovaries [3], and its etiology is related to elevated insulin resistance and obesity in genetically predisposed women [6–9]. Accordingly, 50–75 % of women with PCOS are obese in North America [10]. Obesity increases the risk of PCOS, but it has also been associated with reduced fertility even in ovulatory women [11–13]. As of 2008, 44 % of Canadian women of reproductive age (20 to 44 years) were reported as being overweight (body mass index (BMI) 25.0 to 29.9 kg/m^2^, 25 %) or obese (BMI ≥30.0 kg/m^2^, 19 %) [14]. Also, a survey in Scotland found a significantly higher proportion of obesity in infertile women [15].

Obesity increases the costs of fertility treatments and reduces their effectiveness. Indeed, pharmacological induction of ovulation is less effective in obese PCOS women [16], with the ovulatory dose of clomiphene being positively correlated with BMI [17]. Obesity delays time to conception when using intrauterine donor insemination [18] and reduces conception following assisted reproductive technologies (ART) [19], with higher required doses of gonadotropins [20], lower implantation and pregnancy rates [20–22], and higher miscarriage rates [20–23]. In addition to fertility disorders, obesity increases significantly the risks of many complications of pregnancy, such as gestational diabetes, pre-eclampsia, caesarean section, intrauterine death, which are further increased in morbidly obese women [24–26]. During the postpartum period, overweight mothers are more likely to have hypertension and thromboembolism, leading to a higher risk of maternal mortality [27]. Obesity has also been associated with an increased risk of birth defects, such as ventral wall, neural tube, cardiac and multiple congenital defects [28]. Pregnancy and delivery procedures in obese women are therefore more costly, mainly because of increased caesarean section rates, length of hospital stay and admission to neonatal intensive care [29–31]. It was estimated that the overall costs of fertility treatments and pregnancy complications were increased by 44–54 % and 70–100 % in overweight and obese women, respectively, compared to their normal weight counterparts [32]. Moreover, offspring from obese women are more likely to develop obesity, type 2 diabetes (DM2) and cardiovascular diseases in their lifetime, often at a younger age [33]. Studies suggest that maternal obesity, *via* a pro-inflammatory milieu, insulin resistance, or other hormonal factors [33, 34], modify the in utero environment and might induce fetal epigenetic programming [35] which predisposes to the development of obesity and DM2 early in life, thus perpetuating the vicious circle of obesity and its comorbidities in subsequent generations.

### Obesity management in women seeking fertility treatment

Collectively these substantive maternal and fetal risks call for women to lose weight prior to assisted conception in order to improve their fertility and chance of a healthy pregnancy [22, 36]. Indeed, it has been shown that a supervised lifestyle modification program, including support in addition to diet and exercise advice, can reduce weight, increase ovulatory frequency and improve pregnancy rates [37–39]. Even a modest weight loss of 5–10 % of total body weight can restore ovulation [40, 41]. The Fertility Fitness Program founded by [name] in Australia is a 6-month program of weekly group sessions targeting behavioural changes that include exercise and diet. Clark et al. [39] found that in overweight, infertile, anovulatory women, this program resulted in an average weight loss of 6.3 kg, a restoration of ovulation in 12 of the 13 subjects and pregnancy in 11 women. In a follow-up study, 67 anovulatory obese women who completed the program lost an average of 10.2 kg with 90 % of them resuming spontaneous ovulation [38]. Of these participants, 78 % achieved a pregnancy and 67 % a live birth [38]. Recently, a randomized controlled trial (RCT) was completed in Australia with 171 obese infertile women and demonstrated that the program induced greater weight loss than the control intervention (4.7 vs. 1.3 kg, *P* < 0.001) and increased pregnancy rates at 18 months from 21 to 61 % (*P* < 0.001) (Clark et al., unpublished).

A study conducted by our group shows that it is possible for obese women with PCOS to achieve clinically significant and sustained weight loss by following simple advice given in a regular clinical care setting [42]. We retrospectively reviewed weight changes of young obese PCOS women and found that 43 % of 74 women lost ≥5 % of their initial weight after 6–12 months of follow-up. Young obese PCOS women seem to be a responsive population to lifestyle modification and it is thus expected that an integrated interdisciplinary lifestyle program will be even more effective in a similarly young population of obese women who are also highly motivated by their desire for a healthy baby.

Effective and acceptable lifestyle-modification strategies have the highest potential to result in a reduction in the socioeconomic burden of the obese pregnant woman. Indeed, the American Society for Reproductive Medicine [43], the American Dietetic Association [44], the American Society for Nutrition [44], the European Society of Human Reproduction and Embryology [45] and the British Fertility Society [46] have recommended that overweight/obese women should be provided with assistance to lose weight prior to conception and maintain a healthy lifestyle to prevent excess weight gain during pregnancy. The “Canadian clinical practice guidelines on the management and prevention of obesity in adults and children” emphasizes the importance of the multidisciplinary health care team for effective weight management [47]. After assessment of co-morbidities and readiness to change, a lifestyle modification program is proposed as the first step with an objective of 5–10 % weight loss. Our group implemented an interdisciplinary approach to obesity management at the *Centre hospitalier universitaire de Sherbrooke* (CHUS) since 2001. We have demonstrated in the general obese population that this low-cost approach leads to clinically significant weight loss [48–50]. However, access to our specialized programs is limited by a long waiting list with prohibitive delays for obese women seeking fertility treatment. They require rapid access to a lifestyle program tailored to their specific needs. At this time, there is no integrated lifestyle modification program targeting this specific population in the North American public health care systems. There are gaps in knowledge regarding the benefits and cost-effectiveness of such intervention in the North American context that our study will address. The development of a new initiative aiming at increasing efficiency and reducing the costs of fertility treatments, while improving the health of mothers and their offspring is needed.

### Hypothesis

We hypothesize that an interdisciplinary lifestyle intervention taking place before and during pregnancy in obese infertile women will: 1) improve fertility, efficacy of fertility treatments, and health of mothers and their children; and 2) reduce the cost per live birth and costs of fertility treatments and rates of adverse pregnancy outcomes. We further propose that our research program will 3) result in generalizable and transferable new knowledge useful for decision-makers of the health care system.

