### Study participants

Study participants will be recruited among all women consulting at the CHUS fertility clinic. The staff will assist the research team in identifying potential participants. To be included in the study, women must fulfill the following inclusion criteria: 1) infertility; 2) aged between 18 and 40 years; and 3) obesity (BMI ≥30 kg/m^2^) or overweight if PCOS (BMI ≥27 kg/m^2^). Women will be excluded if they had bariatric surgery or plan for it and/or if natural conception is impossible or highly unlikely (tubal factor, severe male factor infertility, etc.). Infertility will be defined as: 1) failure to achieve a clinical pregnancy after 12 months or more of regular unprotected sexual intercourse in women who are under 35 years with regular menstrual cycles; 2) women who do not have regular menstrual cycles, or are older than 35 years and have not conceived during a 6-month trial period; or 3) women with a known cause of infertility. Eligible patients will be referred to the research coordinator to obtain their individual informed consent prior to baseline data collection.

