### Intervention

#### Control arm

Participants assigned to the control group will receive standard fertility treatments, which will be initiated as soon as clinically indicated. Standard fertility treatments may include lifestyle counselling by the obstetrician-gynecologist certified in gynecologic reproductive endocrinology and infertility (GREI), reproductive endocrinologist or fertility specialist in charge of the care of the patient.

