#### Intervention arm

Participants allocated to the intervention group will be invited to participate in the interdisciplinary lifestyle intervention and will have to delay other fertility treatments for six months. After 6 months of lifestyle intervention alone, women who are not pregnant will begin pharmacologic fertility treatments, as indicated, in conjunction with the lifestyle intervention that will continue to be offered. The aim of the intervention will be to implement progressive and sustainable lifestyle changes in order to reach a modest weight loss. Women will be invited to individually meet with a dietitian and a kinesiologist (20–30 min each) at 0, 3, 6 weeks and then every 6 weeks over a period of 18 months or until the end of pregnancy. A follow-up phone call/email will also take place once between each meeting for additional support. The dietitian will use 3-day food records to evaluate the women’s food intake throughout the program. To help improve patient’s diet, Canada’s Food Guide and the “Healthy Plate” [51] will be the main tools use for nutritional counselling. The kinesiologist will be responsible for taking anthropometric measures and vital signs and for coaching women to increase their physical activity level. A pedometer will be offered to assist the patient. Patients will be guided by the dietitian and the kinesiologist to formulate S.M.A.R.T goals (specific, measurable, attainable, realistic, and timely) at each meeting. The members of our interdisciplinary team will be trained in motivational interviewing. This training can positively affect the attitude to behaviour change in obese infertile women [52].

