### Evaluation of clinical outcomes of the lifestyle program for obese infertile women (Objective 2)

The **primary outcome** will be live-birth rates at 18 months. **Secondary outcomes** will be sub-divided into four categories of clinical outcomes:***Lifestyle and anthropometric outcomes***: evolution of anthropometric measures, changes in lifestyle habits (diet, exercise, sleep, alcohol, and tobacco), physical fitness level, daily energy expenditure from physical activities, time spent in various physical activity intensities, step count, evolution of readiness for change, quality of life.***Fertility outcomes***: pregnancy rate (biochemical pregnancy confirmed by a positive beta-human chorionic gonadotropin (β-hCG) level in the serum), spontaneous abortions, multiple pregnancies, spontaneous vs. ART-induced pregnancy, doses of fertility medications, number of treatment or IVF cycles.***Pregnancy adverse outcomes***: gestational diabetes, hypertension, pre-eclampsia, thromboembolism, caesarean section.***Neonatal outcomes***: birth weight, hypoglycemic episodes, Apgar score, jaundice, admission to neonatal intensive care, congenital defects, intrauterine death.

The results obtained at the CHUS will also be compared to those of women with the same criteria who will be seen in three fertility clinics across Canada. At the CHUS, primary and secondary outcomes will be determined using patients’ assessments, questionnaires and review of patients’ records. At the comparative clinics, charts of patients seen during the same time period will be retrospectively reviewed, and administrative data will be gathered.

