### Data analyses and interpretation

For objectives 1–2, all comparisons between randomized groups at the CHUS will follow both the intent-to-treat and/or per-protocol principles, and will consider results at the end of study. For repeated measures, the last-observation-carried-forward method will be used for women who drop out or become pregnant (depending on analyses). Time-to-event analyses will also be performed for fertility outcomes, with censoring for drop out alone, as well as for anthropometric outcomes, with censoring for both drop out and occurrence of pregnancy. Univariate analyses will compare the change in a variable in the intervention group with the change in this variable in the control group, using two-tailed unpaired *t* tests (for continuous variables) and chi-square or Fisher’s exact tests (for categorical variables). Changes in weight will also be compared for the same follow-up duration with changes for women seen at the other fertility clinics, using ANOVA tests. For the other variables, only end-of-study comparisons will be performed between the two groups in Sherbrooke and the three other fertility clinics, using ANOVA tests (for continuous variables) and logistic regressions (for categorical variables). Bonferroni-corrected p-values will be performed to adjust for the multiplicity of comparisons and an α level of 5 % will be considered significant for all analyses. Continuous variables that are not normally distributed will be log-transformed in order to ascertain normal distribution. Multivariate analyses will also be used in order to adjust for baseline differences and for potential confounders, and to determine independent predictors of outcomes. Triangulation will be performed between quantitative and qualitative data.

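### Hypothesis 1 claims better efficacy of fertility treatments, but the design contains no randomised comparison that measures it

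*Protocol article*

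**What the plan says.** The Abstract and the Hypothesis section both predict that the programme will "improve fertility, efficacy of fertility treatments, and health of mothers and their children". Treatment efficacy is thus a separate item beside fertility.

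The arms reach treatment by different routes. Under Control arm, women receive "standard fertility treatments, which will be initiated as soon as clinically indicated". Under Intervention arm, women "will have to delay other fertility treatments for six months", and then: "After 6 months of lifestyle intervention alone, women who are not pregnant will begin pharmacologic fertility treatments, as indicated".

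The listed fertility outcomes closest to treatment efficacy (Objective 2) are "spontaneous vs. ART-induced pregnancy, doses of fertility medications, number of treatment or IVF cycles". Data analyses and interpretation says that "all comparisons between randomized groups at the CHUS will follow both the intent-to-treat and/or per-protocol principles", at end of study, with multivariate adjustment for baseline differences and potential confounders. The limitations in the Discussion do not mention who gets treated in each arm.

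**The concern.** Response to treatment can be observed only in women who are treated. In the programme arm, being treated depends on not having conceived in six months, which is an outcome after randomisation that the programme is meant to change. Treated programme women are therefore the remainder after the early conceptions, while treated controls are close to the full randomised group. Adjusting for baseline variables does not restore the comparability lost after baseline.

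The alternative is to count doses and cycles over all randomised women. That keeps the randomisation but answers a different question, because a woman who is delayed or never treated adds fewer cycles and less drug however well treatment works.

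The two readings err in opposite directions. Among treated women a real gain could be hidden or reversed. Over all women, lower use could be taken for better efficacy. The choice between them could decide what is concluded on this hypothesis.

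**Working it through.** **The plan's own figure.** The only calculation in the article is for live birth in the randomised groups. With 25 % against 50 %, two-sided α 5 % (sidedness assumed) and power 80 %:

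n = [1.96·√(2·0.375·0.625) + 0.842·√(0.25·0.75 + 0.5·0.5)]² / 0.25² = 57.7, so 58 per group (power 80.2 %).

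Adding 10 % gives 116 × 1.10 = 127.6, so 128. The stated figures reproduce. No figure is given for treatment efficacy.

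**Are the conditions for selection present?**
- *Early conception.* Study participants excludes women "if natural conception is impossible or highly unlikely", so some conceptions in months 0–6 are expected even without a programme effect. The Background also cites a 6-month programme after which 78 % of completers achieved a pregnancy.
- *Heterogeneity.* The clinic treats a range of reproductive problems, and PCOS and non-PCOS women are both enrolled.
- *Meaning of efficacy.* The Background describes reduced effectiveness in obese women through drug doses and through conception, implantation and pregnancy rates after treatment. All of these exist only in treated women.

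The article quantifies neither fecundability nor its spread, so every input below is an assumption.

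**Model 1: shared frailty, no programme effect.** A factor z follows a Gamma distribution with mean 1 and variance v. Treated success per cycle is 0.12·z. Natural monthly success is h·z, with h set so that a chosen share conceives in six months. If S is the share not pregnant at month 6, the mean of z among them is approximately S^v.

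| Conceived by month 6 | S | S^0.5 | S^1 | Simulated ratio, v = 0.5 | Simulated ratio, v = 1 |
|---|---|---|---|---|---|
| 15 % | 0.85 | 0.92 | 0.85 | 0.92 | 0.85 |
| 25 % | 0.75 | 0.87 | 0.75 | 0.86 | 0.74 |
| 35 % | 0.65 | 0.81 | 0.65 | 0.80 | 0.64 |

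At 25 % early conception, first-cycle success is 12.0 % in controls and 12.0 × 0.86 = 10.3 % or 12.0 × 0.74 = 8.9 % in treated programme women. That is 14 to 26 % lower with no true effect. A true gain of 1/0.86 − 1 = 16 % to 1/0.74 − 1 = 35 % per cycle would show as no difference.

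**Weaker correlation.** Here z acts identically on natural and treated conception. With a correlation of 0.5 instead, the 14–26 % shortfall falls to roughly 7–13 %.

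**Model 2: different distribution, no programme effect.** Natural monthly fecundability is Beta distributed, treatment triples it, controls start at month 0 and programme women at month 6 if not pregnant. Pregnancy within six treated cycles, among treated women:

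| Mean, CV | Control | Programme |
|---|---|---|
| 5 %, 1 | 49.1 % | 41.6 % |
| 3 %, 1.5 | 30.6 % | 24.3 % |
| 3 %, 1 | 36.4 % | 32.3 % |
| 1 %, 0.5 | 16.4 % | 16.2 % |
| 3 %, 0 | 43.2 % | 43.2 % |

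The direction is the same, and the gap vanishes without heterogeneity. Because the number of cycles is equal, this is not the effect of unequal treatment time.

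**Counting over all randomised women.** In Model 2 at mean 3 %, CV 1, treated cycles per randomised woman to month 18 are 10.8 in controls and 7.3 in the programme arm, again with no effect. The drop comes from delay and non-treatment.

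**The case against.** The strongest reply is that no endpoint among treated women is actually planned. The article lists doses, cycles and type of pregnancy, not pregnancy per cycle or per treated woman. Objective 2 speaks of impact on fertility, pregnancy and neonatal outcomes without repeating treatment efficacy. Intent-to-treat is named, and time-to-event analyses of fertility outcomes censor for drop-out alone. Doses and cycles over all randomised women are a valid contrast that suits the cost aims, and a separate analysis plan might define the hypothesis more closely.

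Much of this stands. A reader might infer that the trial has committed itself to a biased comparison of treated women; the article does not show that. A reader might also infer that bias arises whatever the population; it needs both varying fecundability and early conception that predicts treated success. The 14–26 % figure rests on perfect correlation between natural and treated success, which is near the worst case, since treatment may bypass the barrier to natural conception.

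What does not stand is that this leaves the hypothesis testable. The hypothesis and the treatment rule together leave no randomised contrast that isolates treatment efficacy. An analysis plan could choose between the two readings but could not make either one measure it. The words and/or per-protocol also leave the analysis set open.

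**Conclusion.** The concern holds as a limit on what can be claimed. Comparisons among treated women are selected after randomisation. Comparisons over all randomised women measure the strategy, not treatment efficacy. Neither supports that part of hypothesis 1.

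The size is uncertain because the article gives no inputs. Under shared frailty (variance 0.5 to 1) and no true effect, the spurious shortfall in first-cycle success is 14–26 % at 25 % early conception, and 8–36 % over early conception of 15 to 35 %. It is about half as large at a correlation of 0.5, and near zero when early conception is rare or women differ little.

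A reader might extend this to the main result. That is not supported: live birth at 18 months in the randomised groups, and its sample size, are untouched by this selection.

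**What to change.** 1. In the Abstract and the Hypothesis section, stop presenting efficacy of fertility treatments as a hypothesis tested by the randomised comparison. Rest the fertility claim on pregnancy and live birth in all randomised women.
2. Interpret doses and cycles over all randomised women as a strategy effect, that is, resource use.
3. Report dose and pregnancy per started cycle among treated women as descriptive and non-randomised.

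Do not try to repair the comparison with a landmark analysis of women in each arm not pregnant at month 6. Controls at that point may already have failed treated cycles, while programme women have failed none. In Model 1 with 25 % early conception, no true effect and six treated control cycles assumed, later per-cycle success is 10.3 % programme against 8.5 % control (v = 0.5) and 8.9 % against 6.5 % (v = 1). From unrounded values that is a spurious programme advantage of 22 to 36 %. Baseline covariates do not capture treatment already failed.

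The cost is wording plus a descriptive table from outcomes already listed. The small downside is that one secondary hypothesis is no longer claimed as a randomised result.
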